## Abstract

**Background:**

Physical activity has established health benefits, but motivation and adherence remain challenging.

**Objective:**

We designed and launched a three-arm randomized trial to test artificial intelligence technology solutions to increase daily physical activity in cancer survivors.

**Methods:**

A single-center, three-arm randomized clinical trial with an allocation ration of 1:1:1: (A) control, in which participants are provided written materials about the benefits of physical activity; (B) text intervention, where participants receive daily motivation from a fully automated, data-driven algorithmic text message via mobile phone (*Coachtext*); and (C) Voice Assist intervention, where participants are provided with an in-home on demand autonomous Intelligent Agent using data driven Interactive Digital Voice Assist on the Amazon Alexa/Echo (*MyCoach*).

**Results:**

The study runs for 5 weeks: a one-week run-in to establish baseline, followed by 4 weeks of intervention. Data for study outcomes is collected automatically through a wearable sensor, and data are transferred in real-time to the study server. The recruitment goal is 42 participants, 14 in each arm. Electronic health records are used to prescreen candidates, with 39 participants recruited to date.

**Discussion:**

This study aims to investigate the effects of different types of intelligent technology solutions on promoting physical activity in cancer survivors. This innovative approach can easily be expanded and customized to other interventions. Early lessons from our initial participants are helping us develop additional advanced solutions to improve health outcomes.

**Trial Registration:**

Retrospectively registered on July 10, 2017 at ClinicalTrials.gov: NCT03212079; https://clinicaltrials.gov/ct2/show/NCT03212079 (Archived by WebCite at http://www.webcitation.org/6wgvqjTji)

## Introduction

There is consistent evidence that identifies poor dietary choice and physical inactivity as major contributors to death in the US and worldwide [1-3]. Physical activity promotion and adverse health behavior prevention strategies can improve health and reduce subsequent disease for individuals and populations [4]. Despite this evidence, only a fraction of the U.S. population adheres to the recommended guidelines [5]. Behavioral interventions for lifestyle modification (walking) have been successful in research settings [6], but translating complex research interventions, particularly in physical activity, into practice remains problematic [7,8].

Recent advances in hardware technologies, statistical methods, big data processing, and cloud-based computing have resulted in artificial intelligence technologies that may offer efficient, low cost and potentially scalable solutions to deliver individualized behavioral interventions to at-risk populations. Further, the development of intelligent technology solutions via ecological momentary assessment provides unique opportunities for behavioral intervention at the individual level, which may increase adherence and promote long-term lifestyle change after the intervention is completed. To test the utility of such technology, our team constructed artificial intelligent agents (IA) to help cancer survivors become more active throughout their daily routines, via a technology-driven clinical trial designed to deliver affordable, scalable, easy to adopt, individualized behavioral interventions. Currently, the IA approach is being tested in a three-arm randomized trial: The Physical Activity by Technology Help (PATH). The trial compares the two technologies—a voice activated intelligent agent and a more traditional intelligent text messaging—compared to a self-driven traditional behavior change (control). The aim of this pilot study is to assess the preliminary effect of a 4-week intervention by different technological approaches to increase daily physical activity, defined as walking (eg, 10,000 steps per day), among overweight and obese cancer survivors, with a special interest in under-represented African American women, in the state of Maryland. In addition, we developed an innovative approach to identify study candidates from review of Epic Electronic Medical Records (EMR). While this IA is specific to cancer survivors, the methods and technology design may be replicated in the general population.

## Methods

### Design

This is a three-arm single center pilot randomized trial with allocation ratio of 1:1:1. The arms are: (A) control, in which participants are provided with written materials about the benefits of physical activity; (B) text-messaging intervention, where participants receive multiple motivational messages from an automated, data-driven algorithmic text message program via mobile phone (*Coachtext*); and (C) voice-assist intervention, in which participants are provided with an in-home autonomous Intelligent Agent using data driven Interactive Digital Voice Assist on the Amazon Alexa/Echo (*MyCoach*).The trial duration is 5 weeks – a one-week run-in phase to establish baseline physical activity, followed by 4 weeks of intervention (Figure 1). Physical activity outcomes are captured via wearable sensors (Fitbit Charge 2 HR). Table 1 includes a schedule of enrollment, interventions, and assessments.

**Figure 1 figure1:**
[figure not shown]
Physical Activity by Technology Help (PATH) study design.

**Table 1 table1:** Physical Activity by Technology Help (PATH) schedule of enrollment, interventions, and assessments.

Study’s activities		Study period								
		Enrollment	Allocation	Postallocation					Close-out	
		*-t*_1_	0	*t*_1_	*t*_2_	*t*_3_	*t*_4_	*t*_5_		*TBD*
**Enrollment**										
	Eligibility screen	X								
	Informed consent	X								
	Allocation and wearable installation	X	X							
	Alexa Installation			X						
**Interventions**										
	Control				X	X	X	X		
	Coachtext				X	X	X	X		
	MyCoach				X	X	X	X		
**Assessments**										
	Individual characteristics	X	X							
	Baseline physical activity			X						
	Outcomes				X	X	X	X		
	Analysis and reporting									X

### Participant Inclusion and Exclusion Criteria

Participant inclusion criteria are: (i) adult cancer survivors residing in the State of Maryland who have had one or more of the cancers of interest (breast, prostate, colon, lung, cervical, oral, melanoma); (ii) completed active cancer treatment (surgery, chemotherapy and/or radiation) at least three months prior to enrollment, with the exception of anti-hormonal therapy; (iii) overweight or obese (BMI 25 and above) status; (iv) internet access at home via Wi-Fi; (v) access to an Android or Apple smartphone; (vi) ability to perform low-intensity daily steps (walking), with physician approval; (vii) less than 150 minutes per week of physical activity reported during the previous four weeks; (viii) willingness to wear an accelerometer; and (xi) willingness to consent and accept randomization. Due to disparities of cancer survivorship among minority groups [9,10], the study is focusing the recruitment activities to target African American cancer survivors.

Exclusion criteria are: (i) reported engagement in, or more than, 150 minutes per week of physical activity during the previous four weeks (The Godin-Shephard Leisure-Time Physical Activity Questionnaire) [11-13]; (ii) plans to relocate or travel during the course of the intervention; (iii) stage 4 cancer diagnosis; (iv) current use of a physical activity tracker or engagement in a structured physical activity program; (v) participation in another study that may interfere with our outcome of interest; (vi) an unstable mental condition that would prevent performing the study activities and requirements; and (vii) current or planned pregnancy.

### Innovative Recruitment

Participants are recruited using both passive and active strategies. In the *passive strategy*, the study team distributes flyers at the Johns Hopkins outpatient oncology clinics, patient education rooms, survivorship clinics, and survivorship meetings to spread study awareness among clinic staff, particularly nurse educators and managers. With the *active strategy* for recruitment, the Epic reporting function is used to generate patient lists of those who match the screening criteria at selected Johns Hopkins clinics in Maryland. Screening for existing cancer patients takes place at the outpatient clinics, by specific providers and on follow-up weekly appointments only; potential participants must have a prior diagnosis of a cancer of interest, a BMI of 25 or above, and reside in the state of Maryland. Once a list is generated, the study team actively reaches out to each patient after the outpatient clinic visit to provide them with study information. All candidates identified by either strategy are included in an electronic Clinical Research Management System (CRMS) linked to the EMR. The study coordinator updates the candidate’s status regularly based on candidate eligibility, consent, and enrollment type. Reasons for ineligibility are also recorded in CRMS. Data on the number of eligible patients, along with reasons for not enrolling can be captured and reported to the institution’s Institutional Review Board (IRB). Weekly automated reports can be generated from CRMS to track enrollment and pending statuses.

Once eligibility is determined, an IRB-approved consent designee obtains an IRB-approved written informed consent form (ICF) in the outpatient clinic or at the study office. A signed and dated IRB-approved ICF is documented in a secure participant study file prior to initiating study-related procedures. As part of the consent process, the study team 1) informs each participant of study procedures and requirements and allows sufficient time for the individual to decide whether to participate in the study; 2) answers questions about the details of the study; and 3) ensures that the ICF is approved by the IRB when an amendment to the study protocol is made. Participants are free to withdraw consent for participation in the study at any time, without affecting their current or future treatment.

### Sample Size

The investigators designed this study to compare: (i) a dialogue Intelligent Agent, using data driven Interactive Digital Voice Assist on Amazon Alexa/Echo speaker (*MyCoach*) in assisting participants in increasing their physical activity, with (ii) a text messaging intervention and (iii) a written information/self-motivation intervention. To detect at least a 2000 step difference in means at a SD of 1800 steps/day (the standard deviation of the 28-day daily sample mean is 1800 steps), with a 2-sided alpha of 0.05, and power of 0.8, or 80, 13 participants are required per arm (39 participants total (with Bonferroni correction of 2 comparisons)). To account for intention to treat and possibly per-protocol analysis, the study team subsequently added an additional participant to each arm; therefore, 14 participants are being recruited per arm, for a total of 42 participants. Also, to account for dropout, the protocol also allows the addition of patients to replace those who dropout due to a condition/illness that prevents them from participating in the trial during the run-in period.

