### Statistical Analyses

As the primary outcome variable is the 4-week change from the baseline in the average number of steps per day, the primary analysis will use a two-sample t-test to compare each active intervention arm with the control arm based on intent-to-treat strategy. A Bonferroni correction will be used to adjust for multiple comparisons.

For the secondary outcomes (activities bouts, fragmentation, and patterns), a linear regression model will be fitted for the 4-week change from the baseline in the number of steps and duration of activity bouts each day. The independent variables include the baseline number of steps, study arm (modeled by two dummy variables for the two active treatment arms, and the control arm is treated as reference group), and any potential baseline confounding factors. Poisson regression will be used to analyze the total number of activity bouts, fragmentation indices, and variability indices. The independent variables include baseline number of steps, study arm, and any potential baseline confounding factors as the independent variables. In all analyses, data will be properly transformed to fit the model assumption before regression analysis. Although missing data is not anticipated to be a challenge, small amount of non-wear time for charging, bathing, etc. will have minimal effects on the primary study aim since it depends on the average steps across the intervention period. Since Stratified Permuted Block Randomization is being employed, we will consider minimization to balance interventions simultaneously over several prognostic factors to ensure equal distribution across arms. To date nearly 80% of the target population has been enrolled, and only one participant stopped wearing the tracker one day a week for religious reasons.

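### The design statement names MyCoach against text, but the primary analysis compares only each active arm with control, so voice versus text has no specified test

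*Protocol article*

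**What the plan says.** Three places in the protocol article bear on which arms are compared.

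- **Sample Size.** MyCoach is the index arm, to be compared "in assisting participants in increasing their physical activity, with (ii) a text messaging intervention and (iii) a written information/self-motivation intervention". The next sentence gives 13 per arm "with Bonferroni correction of 2 comparisons", later raised to 14. The two comparisons are not listed.
- **Statistical Analyses.** For the primary outcome, "the primary analysis will use a two-sample t-test to compare each active intervention arm with the control arm based on intent-to-treat strategy". Then: "A Bonferroni correction will be used to adjust for multiple comparisons". The number of tests is not stated, but two follow from the pairs named. In the regression for secondary outcomes, "the control arm is treated as reference group", and no contrast between the two active arms is specified.
- **Introduction.** "The trial compares the two technologies", and the same sentence goes on to say that they are "compared to a self-driven traditional behavior change (control").

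**The concern.** Read literally, Sample Size points to MyCoach versus text and MyCoach versus control, while Statistical Analyses points to Coachtext versus control and MyCoach versus control. A reader cannot tell whether voice versus text is a confirmatory question, a secondary one, or not a question of the trial at all.

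At stake is which hypotheses are confirmatory. If the analysis follows Statistical Analyses, the first comparison named in the design statement is never tested. If someone later adds it because the design statement names it, the correction for two comparisons no longer fits the number of tests made.

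**Working it through.** **1. Pairs side by side** (A control, B Coachtext, C MyCoach)

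| Pair | Sample Size, read literally | Primary analysis |
|---|---|---|
| C versus A | yes | yes |
| C versus B | yes | no |
| B versus A | no | yes |

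Each column has two pairs, and their union has three.

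**2. The plan's own figure.** Inputs from Sample Size: difference 2000 steps, SD 1800, two-sided alpha 0.05, power 80%. Normal approximation: n per arm = 2(z₁₋α/₂ + z₀.₈)²(SD/difference)², with 2 × (1800/2000)² = 1.62.

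- Alpha 0.05: 1.62 × (1.960 + 0.842)² = 12.7, so 13. This is the stated figure.
- Alpha 0.025 (Bonferroni for two): 1.62 × (2.241 + 0.842)² = 15.4, so 16 (17 by the exact t-test).
- Alpha 0.0167 (Bonferroni for three): 1.62 × (2.394 + 0.842)² = 17.0, so 17 (19 by the exact t-test).

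The choice between the two sets of pairs does not change n: any two pairs at 0.025 need the same number. That 13 matches the uncorrected alpha is a separate matter and is not part of this point.

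**3. Familywise error with all three means equal** (simulation, 14 per arm, two-sample t-tests)

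- The two active-versus-control tests at 0.025 each: 4.7%.
- All three pairs at 0.025 each: 6.5%.

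A known-variance simulation agrees: 4.6% for two pairs that share an arm, whichever two are chosen, and 6.4% for all three. With the third pair added at an uncorrected 0.05 the figure is 8.5%. With all three at 0.0167 it is 4.4%.

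**4. Power at 14 per arm, SD 1800.** For one t-test at 0.025 the noncentrality is (2000/1800) × √(14/2) = 2.94 on 26 degrees of freedom, which gives 71%. Simulated power for MyCoach versus control:

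| Means (A, B, C) | Bonferroni for two | Holm for two | Closed three-arm test |
|---|---|---|---|
| 0, 2000, 2000 | 71% | 77% | 77% |
| 0, 0, 2000 | 71% | 71% | 77% |
| 0, 1000, 2000 | 71% | not needed here | 71% |

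The closed test is a global test of arm at 0.05 followed, if significant, by each pairwise test at 0.05 from the common three-arm model. Its familywise error is 5.0% to 5.1%. With means 0, 0, 2000 it also gives 77% for MyCoach versus Coachtext. Bonferroni for three gives 65% per pair at 2000 steps.

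**The case against.** The strongest reply is that there is only a loose sentence here. Sample Size lists the three arms and states no hypotheses. It never names its two comparisons, and two fits each active arm against control just as well. The control-referenced regression points that way, and so does the Introduction when its sentence is read to the end. The operative analysis is the one in Statistical Analyses, and its error rate is controlled. In a pilot, leaving voice versus text outside the confirmatory family is an ordinary choice.

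Most of this stands. That the two Bonferroni comparisons are MyCoach versus text and MyCoach versus control is an inference from the neighbouring sentence and the matching count. The Introduction gives no firm support for a head-to-head comparison. A reader might infer that the plan inflates the familywise error to 6.5%. The documents do not support that, because nowhere do they plan three tests at 0.025. Bonferroni for two is also valid, so replacing it is an improvement and not the correction of an error.

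What the reply does not remove is that the design statement makes MyCoach the arm compared with text, and the primary analysis contains no such comparison. Both statements are in the article, so this is not detail left to a fuller document.

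**Conclusion.** The point holds as an inconsistency about which comparisons are confirmatory. Sample Size and Statistical Analyses share one pair and differ on the other, and MyCoach versus Coachtext has no specified test.

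Its size is limited. The primary analysis as written holds the familywise error at about 4.7%, and the mismatch alone changes neither that error nor the required n. The exposure is conditional: about 6.5% if all three pairs are tested at 0.025.

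The error rates assume equal group sizes of 14, normal data and a common variance. The power figures also assume the plan's own 2000 steps and SD 1800. Holm's gain is largest when both active arms work and close to nil when only one does.

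**What to change.** 1. In Sample Size, state that the two confirmatory comparisons are Coachtext versus control and MyCoach versus control, as in Statistical Analyses.
2. Label MyCoach versus Coachtext as a secondary contrast outside that family.
3. Replace Bonferroni with Holm for the two primary tests: the smaller p-value against 0.025 and, if it is significant, the larger against 0.05. This keeps the 5% familywise error and is never less powerful than Bonferroni.

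The cost is wording and no additional participants. It should be done while the data analyst is still blinded. The small downside is that confidence intervals matched to Holm are less simple than Bonferroni intervals.

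If the sponsor wants voice versus text to be confirmatory, the closed three-arm procedure is a valid alternative that covers all three pairs. It is a trade-off: it replaces the planned two-sample tests with a common-variance model, its matching intervals are also less simple, and its power advantage over Bonferroni for two depends on the pattern of effects (77% against 71% when only MyCoach works, no gain with means 0, 1000, 2000).

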### Randomization

Participants are randomized with an allocation ratio of 1:1:1 to the control self-driven arm (Group A), *Coachtext* (Group B), or *MyCoach* (Group C). Once a participant signs the IRB approved ICF, the randomization procedure is conducted. Since the study is recruiting cancer survivors, the team collects data regarding certain prognostic factors that may affect physical performance and thus ability to perform physical activity, including 1) types of cancer; 2) age; and 3) BMI. To attenuate the impact of such factors the study team is using Stratified Permuted Block Randomization, which generates strata by sex, age group, and BMI, then assigns a unique number for each block. At randomization, the PI or study coordinator assign strata by participant variables, then assign the arm after generating a random number out of all possible blocks using random.org. Subsequent assignment is linked to the strata in which the new participant belongs. If the prior block under the selected strata is completed or not started, a new block is selected/opened using random.org. Only the principal investigator (PI) and the study coordinator are designated to conduct the randomization procedure. The PI or the study coordinator report the randomization procedure to the participant orally and record it on the randomization sheet. The study data analyst is blinded to the random assignments.

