### Blinding

Due to the nature of the study interventions, study participants are not blinded. Data for the principal outcomes, however, are collected using sensors. Therefore, the study data analyst is blinded during data collection and during analysis.

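### The run-in week that supplies the baseline for the primary outcome is measured after open allocation, so any effect of knowing the arm on run-in steps enters the estimated treatment effect

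*Protocol article*

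**What the plan says.** All references are to the protocol article.

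- **Randomization:** "Once a participant signs the IRB approved ICF, the randomization procedure is conducted". The same section adds: "The PI or the study coordinator report the randomization procedure to the participant orally and record it on the randomization sheet".
- **Blinding:** "Due to the nature of the study interventions, study participants are not blinded". Outcome capture by sensor and a blinded analyst are the stated protections.
- **Design:** the trial has "a one-week run-in phase to establish baseline physical activity, followed by 4 weeks of intervention".
- **Table 1:** allocation is marked at enrolment and time 0. Columns t1 to t5 sit under the header "Postallocation". The rows "Baseline physical activity" and "Alexa Installation" are both marked at t1. The three interventions and the outcomes are marked t2 to t5.
- **Study Outcomes:** the primary outcome is the percent change in daily steps from the run-in week.
- **Statistical Analyses:** the primary variable is described as the 4-week change from baseline in average steps per day. Each active arm is compared with control by a two-sample t-test, with Bonferroni correction.

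No section holds back disclosure of the arm until the run-in is over, and none uses a baseline taken before randomisation.

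**The concern.** Randomisation makes the arms comparable on what precedes it. Run-in steps come after it, and walking is voluntary behaviour in volunteers who joined in order to become more active. Someone who knows that a coaching arm has been assigned may start early or may wait for the coaching to begin. Someone who knows that control has been assigned may lose interest or may compensate. Any such difference between arms is treated as baseline and taken out of the treatment effect. It could hide a real effect or create an apparent one, and a larger sample would not remove it.

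Neither stated protection covers this. The sensor records the altered walking faithfully, and the blinded analyst receives it as given. Using run-in steps as a covariate, as the secondary regressions do, does not cure it either, because the covariate is itself measured after allocation.

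**Working it through.** **1. Order of events.** Consent is followed by randomisation, which is reported orally (Randomization; time 0 in Table 1). Baseline steps and Echo installation follow (t1), then intervention and outcomes (t2 to t5). The text and the table agree, so the baseline falls after allocation on the document's own account.

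**2. How a run-in shift enters the estimate.** Let b be the active-minus-control difference in mean run-in steps/day caused by knowing the arm, and let D be the true effect on the 28-day mean.

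- *Absolute change (Statistical Analyses):* expected estimate = D − b. With D = 2000 and b = 500 this is 1500. With b = −500 it is 2500.
- *Percent change (Study Outcomes):* for an active-arm participant whose undisturbed level is B, the result is 100 × [(B + 2000)/(B + b) − 1]. With b = 500 and assumed B of 4000, 5000 and 6000, it falls from 50.0 to 33.3, from 40.0 to 27.3 and from 33.3 to 23.1. The loss is 16.7, 12.7 and 10.2 percentage points, so it depends on B and is not a simple subtraction.

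**3. Inputs for the illustration.**

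| Input | Value | Source |
|---|---|---|
| True effect | 2000 steps/day | Sample Size |
| SD of 28-day mean | 1800 | Sample Size |
| Per arm | 14 | Sample Size |
| Alpha per comparison | 0.05/2 = 0.025, two-sided | Sample Size |
| SD of run-in mean | 1800 | assumed |
| Correlation ρ, run-in with 28-day mean | 0.3 to 0.8 | assumed |
| Run-in shift b | 500 steps/day | assumed |

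The plan's own figure of 13 per arm follows from 2 × (1.960 + 0.842)² × (1800/2000)² = 12.7, that is, at alpha 0.05 without the Bonferroni correction. With alpha 0.025 the same formula gives 2 × (2.241 + 0.842)² × 0.81 = 15.4, so 16. That mismatch is a separate matter and this point does not depend on it.

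**4. Power and false rejection, absolute change.** SD of change = 1800 × √[2(1 − ρ)]; SE = SD × √(2/14). Power is from the noncentral t with 26 degrees of freedom and critical value 2.379.

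| ρ | SD of change | SE | Power, b = 0 | Power, b = 500 | Rejection if D = 0, b = ±500 |
|---|---|---|---|---|---|
| 0.3 | 2130 | 805 | 54.9% | 32.0% | 5.2% |
| 0.5 | 1800 | 680 | 71.1% | 44.3% | 6.3% |
| 0.6 | 1610 | 609 | 81.2% | 54.2% | 7.4% |
| 0.8 | 1138 | 430 | 98.5% | 85.9% | 12.9% |

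**5. Smaller and larger shifts at ρ = 0.5.** Power is 58% for b = 250 and 20% for b = 1000. Rejection with no true effect is 3.4% and 20.0%.

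**6. Comparison that leaves out the run-in value.** SE = 1800 × √(2/14) = 680 and power is 71%, whatever ρ and b are. This equals the precision of the unshifted change score at ρ = 0.5. The 28-day comparison is more precise below that correlation and less precise above it.

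**The case against.** The best defence is that little can happen in the run-in. Table 1 starts every intervention at t2, Coachtext messages begin only after the seven-day run-in, and MyCoach speaks only when asked. All arms receive the same tracker and app and the same 10,000-step target. What is left is anticipation, plus possibly an installed speaker. This stands as a limit on the mechanism, but it does not remove it.

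Two stronger readings are tempting and are not supported. A reader might infer that participants are told their arm at the consent visit. The Randomization section says that the procedure is reported orally but not when, so early disclosure is a close inference. A reader might also infer that the MyCoach arm lives with its device through the whole baseline week. Table 1 marks the week t1 only, and installation at its end fits equally well. The point needs neither reading: the baseline week follows allocation, participants are unblinded, and nothing delays disclosure.

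It is also fair to say that no single power figure can be quoted as the damage. The shift, the correlation and the run-in SD are all assumed, and the result moves widely with the correlation. Likewise, a one-for-one bias applies only to the absolute change.

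Finally, this is a pilot, the randomisation is intact, and a comparison free of the run-in value can be made from data already being collected. That lowers the severity but does not answer the point.

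**Conclusion.** The point holds as a design weakness: the baseline in the primary outcome is a post-allocation measurement in unblinded participants. The order of events is certain. The size and direction of any bias are unknown, and the documents contain nothing that would estimate them.

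Under the assumptions in step 3, a 500-step shift towards the active arm costs about 13 to 27 percentage points of power over correlations of 0.3 to 0.8. With no true effect, a shift of that size in either direction raises per-comparison rejection from 2.5% to between 5% and 13%. A shift in the other direction would enlarge the apparent benefit. This should be fixed, but it does not invalidate the trial.

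**What to change.** Before the blinded analyst is given the arm codes:

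1. Prespecify, as a key sensitivity analysis, a comparison of 28-day mean steps/day between each active arm and control that does not use the run-in value. Keep the same two-sample test and Bonferroni level. The Sample Size section already states the SD for this quantity (1800).
2. Report run-in steps/day by arm, so that readers can see whether the arms had already separated.

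The cost is one added analysis and one descriptive table, with no new data. The sensitivity analysis is less precise than the change score if the run-in to follow-up correlation exceeds 0.5, which is a reason to report both.

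Randomising and installing the Echo after the run-in is the sound order for a successor trial. Here the Trial Status section reports 39 enrolled as of January 2018 against a goal of 42. A change now would reach 42 − 39 = 3 participants, plus any run-in replacements, and would mix two kinds of baseline within one outcome.
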